**Use of linked data**

We will use link to ONS mortality file for our outcome measures. **Data/ Statistical Analysis Plan**

1) We expect that overdose and drug related mortality risk differs by period of treatment exposure (1-4 weeks treatment start, rest of treatment duration, 1-4 weeks treatment end, 5-52 weeks out of treatment). The main analysis will test whether there is evidence of a difference in mortality risk by modality of OST (methadone vs. buprenorphine) at different periods on and off treatment – and will investigate also mortality risk in relation to additional exposures (co-prescription of benzodiazepines, measures of treatment performance/quality) and confounders (age, gender, co-morbidity as defined by Charlson Index(24), alcohol and mental health problems, treatment episode number, calendar year) all of which have been shown to influence mortality risk(11) (9). However, other potential confounders or factors relating to injecting risk may be missing or incompletely measured in CRPD (such as crack-cocaine use).

We will undertake a series of analyses that aim to incorporate and adjust for confounding.

First, we will use Poisson regression incorporating time varying covariates (such as co-prescription of benzodiazepines, episode and duration of treatment) to describe mortality risks and compare these at different periods on and off treatment and by modality of OST. These analyses will generate incidence rate ratios (IRR) that compare mortality risk for patients on methadone (from week 4 to end of treatment as baseline) to other periods and other forms of OST; will compare mortality rate for key confounders (above); adjust IRR by period on or off treatment for these confounders; and examine specifically whether co-prescription of benzodiazpeines increases the risk of mortality during and after treatment.

Second, we will undertake analyses of patient characteristics in order to develop and use propensity scores that can be used to balance buprenorphine and methadone exposure groups and test for differences in mortality risk between the groups(25-27). The primary care databases hold a substantial amount of information on the patients’ diagnoses and treatment history as well as information on the practices – too much data to fit as individual covariates. Therefore, we can use these data to generate propensity score matching in order to use the score to reduce selection bias and match the patients exposed either to buprenorphine or methadone or to short or long term treatment(27).

Third, the problem of confounding (known and unknown) also will be addressed using self-controlled case-series (SCCS) methodology in which patients act as their own controls(28), as has been used in other studies of primary care databases(29, 30). In this method the number of events are classified according to the length of the exposure (in period; in and out of treatment) and an estimate of the hazard or incidence rate ratio is derived by conditioning on the number of events over the exposure history(28). Since there is missing information on risk of death prior to exposure only cases that have been exposed are included in the analysis. In addition, time invariant confounders (such as sex, age, underlying health problems) are controlled for implicitly; and time variant confounders can be fitted within the model. [name] and [name] are extending the SCCS method to deal with finite outcomes such as drug related/overdose death, and exposures that may persist (such as opiate substitution treatment) and this study will be a case study on how SCCS can be used with such exposures and outcomes. SCCS has been used for censored events – such as death previously (31, 32) – but classifying the exposure will require methodological development.

Fourth, even in the absence of unmeasured confounding, conventional methods (eg regression models that control for baseline or time-dependent confounders) will provide estimates that may fail to have a causal interpretation when (i) there is a measured time-dependent risk factor for survival that also predicts subsequent treatment, and (ii) past treatment history predicts the subsequent level of this risk factor. We will use inverse probability (IP) weighted estimation of marginal structural models, which avoids conditioning on time-dependent confounders(33, 34). Instead, we estimate the inverse of each patient’s probability of their observed treatment history at each time. By weighting a marginal model according to the reciprocal of these probabilities, we mimic a situation in which the assignment to treatment is at random (or unrelated to the time-varying covariates).

By examining the intervention effects between exposure and outcome and how they vary across multiple methods which adjust for confounding in different ways we will be able to assess the likelihood that residual/time-varying confounding remains a significant problem, and to contribute stronger evidence on the impact of treatment on drug related mortality(35, 36). Similar analyses will be conducted on the risk of mortality during and after exposure to non-pharmacological treatments(18).

2) The secondary analysis of clinical databases will test whether there have been changes over time in the number of patients treated over time and specifically in the delivery of OST in primary care (e.g. the mean dose, treatment duration, modality and evidence of supervised consumption). Segmented regression techniques will be used for time trend analyses of these treatment indicators in order to test whether there have been changes over time, and whether the timing of the change is consistent with issuing of new treatment guidelines(20, 37).

3) The estimates of the effect of different drug treatments on mortality risk for different periods on or off treatment derived from analyses of Clinical Practice Research Datalink (CPRD) and Drug Data Warehouse (DDW) will be used in differential equation or individual based models that consider the flow of people into and out of drug treatment fitted against estimates of the annual number of drug related deaths in the population. The models will incorporate treatment coverage and extend previous models(11) by including additional factors that may affect the risk of overdose death or duration maintained on treatment in this analysis. This will be decided through consultation with other researchers on the grant and key stakeholders (Public Health England, Bristol Health Integration Team on Addiction) and may include:- modality of treatment, combination of treatments, age, gender, treatment history, benzodiazepine prescription, alcohol abuse, other psychosocial and family therapy (if data on intervention effect are available). An individual based model will be used if it is deemed important to incorporate the full heterogeneity in treatment duration and/or if an individual’s past treatment episodes are shown to effect the duration that they remain on treatment or the mortality rate while on treatment. The model will be parameterized with data from this study, and key uncertainties will be varied in a Bayesian framework to obtain multiple possible model fits to the annual number of drug related deaths in the population at certain times points in the past(38). Model fits will be weighted by their goodness of fit using likelihood measures (39, 39).

The model fits for each time point will be used to firstly evaluate the impact of current and past levels of drug treatment on decreasing drug related deaths in the population (11, 22), with model fits being used to test hypotheses for why the yearly number of overdose deaths has not decreased over the last 10 years while the rate of methadone deaths per gram has decreased. The hypotheses will be incorporated into the model fitting process through assumptions made about the uncertainty ranges or values assumed for specific parameters, and then the likelihood of specific hypotheses will be evaluated through the relative degree to which the model fits the data with that parameter assumption(40, 41).

More importantly the models will then be used to project the likely impact of varying specific current characteristics of drug treatment on the incidence of drug related deaths in the population, such as: combining different treatment modalities, changing treatment duration, controlling concomitant prescription, and introducing interventions to reduce treatment drop-out or relapse following treatment cessation(11, 22). These projections will increase our understanding of the role of different factors in effecting the impact of OST, and the possible impact of future strategies that may attempt to reduce overdose death by altering certain characteristics of drug treatment in the UK. The relative efficiency of these strategies will also be assessed with efficiency being defined in terms of the number of deaths averted per person year on OST. This will help us to assess the likely optimum strategies for reducing the frequency of overdose deaths for specific coverage levels of drug treatment in terms of grams distributed per year.

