**Sample size/power calculation**

The main analysis is on opiate substation treatment (OST) in primary care and risk of death and in particular the comparison of methadone and buprenorphine*.

There will be at least 20,000 OST patients (extracted from CPRD GOLD patients) from 1998 to 2014 linked to NHS central registry and ONS mortality data, that will generate 67,000 person years (pys) follow-up (~32,000 on treatment and ~35,000 off) if censored 12 months after last OST. There will be over 700 deaths of which ~500 will be due to overdose. This will be the largest study in the UK with precise data on OST treatment exposure (including ~ 12000 pys on buprenorphine and 30,000pys on methadone). In addition, there will be approximately 10,000 and 12,000 person years in treatments lasting less than 1 month or greater than 12 months, and 3000 and 1200 person years follow-up in the first 4 weeks treatment on or immediately after methadone or buprenorphine treatment respectively.

Thus, there is sufficient power (> 90%) to determine whether:-

1. there is at least a halving of the risk of death during treatment on burpenorphine compared to methadone (i.e. 0.35% vs. 0.69% respectively) – which requires a sample of at least 922 in each group compared to 12,000 and 20,000 on buprenorophine and methadone
2. and sufficient power (80%) to test if the risk of death is at least a 1/3 lower on buprenorphine at (0.006%) compared to methadone (0.016%) in the first 4 weeks of treatment (1200 and 3000 person years respectively) – as indicated by unpublished analyses by Degenhardt on Australian mortality cohort(9).

In addition, there is sufficient power to corroborate that the risk of fatal overdose out of treatment at 0.8% is twice as high as the risk during treatment – which will require sample of at least 788 in and out of treatment compared to our sample of over 30,000 person years in each group; and that the risk of death in the 4 weeks after treatment at about 4.6% is 1/3 lower (3.0%) for people treated for short duration of treatment (< 1 month) compared to those treated for 12 months or longer – which will require sample of at least 3123 in each group compared to over 3500 and 3850 person years among those exposed to short or prolonged treatment respectively;

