**Exposures, outcomes and covariates**

*Exposure:-* OST includes methadone and buprenorphine and occasionally dihydrocodeine(6, 11). Intervention exposure is defined by prescribing data collected by primary care practices contributing information through their electronic health record systems to the Clinical Practice Research Datalink (CPRD). This will include information on all prescriptions in primary care plus other information on diagnoses and attendances at primary care and hospital. We will extract information on patients on the basis that they have a drug misuse diagnosis and have been prescribed methadone or buprenorphine. Some patients also may have been prescribed dihydrocodeine as OST – and so we will include these treatment episodes as well. The information provided by CPRD will allow us to establish when OST started, changes in dose or type of OST, and when OST ceased. For each treatment period we will classify different periods “on”/during or “off”/after OST or other drug treatment e.g. 1st 2 weeks of treatment, rest of time on treatment (baseline treatment period), 1st 4 weeks after treatment, and rest of time out of treatment (censored at 12 months after last prescription); as well as measure average OST duration and classify treatment duration (≤ 1 month, 2-6 months, 7-12 months, 12+months).

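### Duration of treatment, if entered in classes beside treatment period in the Poisson model, distorts the onset rate ratio: roughly 0.75 to 1.2, at the extreme 1.5, when the truth is 1.00

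*Protocol*

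**What the plan says.** The Data/ Statistical Analysis Plan, item 1, divides follow-up into "1-4 weeks treatment start, rest of treatment duration, 1-4 weeks treatment end, 5-52 weeks out of treatment" and expects overdose and drug-related mortality to differ between these periods. The first analysis is "Poisson regression incorporating time varying covariates (such as co-prescription of benzodiazepines, episode and duration of treatment) to describe mortality risks and compare these" at the different periods and by type of substitution drug. The reference is "patients on methadone (from week 4 to end of treatment as baseline").

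The description of the rate ratios then says the analysis will "adjust IRR by period on or off treatment for these confounders". The list meant by that ends with "alcohol and mental health problems, treatment episode number, calendar year) all of which have been shown to influence mortality risk". Duration of treatment is not on it.

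The exposure section says the investigators will "classify treatment duration (≤ 1 month, 2-6 months, 7-12 months, 12+months"). As an example of periods it gives "1st 2 weeks of treatment, rest of time on treatment (baseline treatment period"), an onset window of two weeks and not four. The protocol does not say whether duration is elapsed time or the completed length of the episode, whether the model uses the classes or a continuous term, or what value duration takes once treatment has stopped.

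The sample-size section assumes that "the risk of death in the 4 weeks after treatment at about 4.6% is 1/3 lower (3.0%) for people treated for short duration" (under one month), compared with people treated for a year or more.

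**The concern.** While a patient is on treatment, the period (weeks 1-4 or later) follows from the time since the start. A duration covariate measuring that same time in classes, the first of which ends at about day 30, leaves almost no on-treatment data to separate an onset effect from a short-duration effect. The model must then take the short-duration effect from off-treatment time, where duration means something else: how long the finished episode lasted. A common effect is harmless only if post-cessation risk does not vary with duration, and the protocol's own planning figures assume that it does.

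Risk at treatment onset is one of the study's listed questions. The period-specific estimates also feed the policy model of drug-related deaths. A distorted onset ratio would carry through to both.

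**Working it through.** **1. The plan's own figure.** The protocol asks for 3123 per group to compare 4.6% with 3.0%. The usual two-proportion formula (two-sided 5%, 90% power) gives n = 2999. With the continuity correction, n' = (n/4)[1 + √(1 + 4/(n·d))]² and d = 0.016: 4/(2999 × 0.016) = 0.0834, √1.0834 = 1.0409, and (2999/4) × 2.0409² = 3123. So the duration contrast is a deliberate planning assumption. Its ratio is 3.0/4.6 = 0.652, inverse 1.53.

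**2. Inputs.** From the sample-size section: 0.69 per 100 person-years on methadone (used for all time on treatment), 3.0 and 4.6 in the 4 weeks after short and long treatment (read as rates per 100 person-years, because the protocol counts these samples in person-years), and 0.8 out of treatment (stated for fatal overdose, used here for weeks 5-52). Assumed: the number of treatments, their mix by duration (for example 40/35/13/12%) and the split of person-years. The true onset ratio is set to 1.00.

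**3. Elapsed duration in classes.** Model: log rate = α + β(period) + γ(duration class). On treatment, every onset day lies in the first class. With classes cut at 28 days, no baseline day does. On-treatment data then inform only the sum β(onset) + γ(first); on their own they give a design of rank 4 for 5 columns. The first-class effect has to come from off-treatment time:

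fitted onset ratio = true onset ratio / exp(γ first, estimated off treatment).

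A calendar-month cut adds only days 29-30. Taking (3000 + 1200) × 13 = 54,600 treatments, or half that, 27,300: 27,300 to 54,600 × 2.4/365.25 = 179 to 359 person-years, × 0.69% = 1.2 to 2.5 deaths.

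**4. Size by hand.** Suppose 52 weeks of off-treatment follow-up and 4.6 for all longer classes. The first 4 weeks weigh 28/365.25 = 0.0767 and the rest 336/365.25 = 0.920.
- Contrast in the first 4 weeks only: short class 0.0767 × 3.0 + 0.920 × 0.8 = 0.966; at the longer-class rates 0.0767 × 4.6 + 0.920 × 0.8 = 1.089. exp(γ) = 0.966/1.089 = 0.887, so the fitted onset ratio is 1/0.887 = 1.13.
- Contrast through the whole off-treatment year: exp(γ) = 0.652, so the fitted ratio is 1.53.

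**5. Model fits to expected deaths, true onset ratio 1.00.**

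| Form of duration | Fitted onset ratio |
|---|---|
| Elapsed classes, contrast in 4 weeks off only | 1.10-1.20 |
| Same, taking the stated 3500 and 3850 person-years as time in that window | 1.39 |
| Elapsed classes, contrast through the off-treatment year | 1.26-1.53 |
| Same, two-week onset window | 1.39 |
| Elapsed, linear | 1.01-1.02 |
| Elapsed, logarithmic | 1.06-1.15 |
| Completed length in classes, death not ending the episode | 1.02-1.10 |
| Completed length in classes, death ending the episode | 0.74-0.85 (0.70-0.78 under other assumed mixes) |
| Duration omitted, or acting off treatment only | 1.00 |

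**6. Why completed length goes the other way.** A death in weeks 1-4 ends the episode and so puts it in the shortest class. The three longer classes, 60% of treatments in the assumed mix (35 + 13 + 12), contribute their first four weeks with no deaths by construction. Completed length therefore conditions on the future, and the onset ratio is pulled below 1.

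**The case against.** The strongest reply is that the harmful model is not written down. Duration appears only as an example among time-varying covariates, and the list used to adjust the period ratios omits it. Exact coding is ordinarily left to the analysis plan, which is not at hand. This stands in part: it is not established that the reported onset ratio will condition on duration. But the same paragraph says that the regression incorporating duration is the one that compares the periods, and the only coding offered is in classes. This is a stated modelling choice that can be read two ways, and the answer changes with the reading.

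A reader might infer that period and duration are the same variable on treatment. The documents do not support that: there are four duration classes and two on-treatment periods, only the first class nearly coincides with onset, and a continuous term has no such overlap. With the two-week window given as an example, weeks 3-4 are baseline time inside the first class and help identification.

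A reader might also infer that the onset ratio will be about 1.5. The sample-size section gives 3.0% against 4.6% only for the 4 weeks after treatment, and only for under one month against a year or more. Reaching 1.5 means carrying the contrast through the off-treatment year and giving the intermediate classes the 4.6 rate. Even there the 95% interval is wide, about 0.85 to 2.75.

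Finally, the key hypothesis is buprenorphine against methadone, and no bias in that contrast has been shown.

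**Conclusion.** The point holds in a limited form. The protocol names time-varying duration as a covariate in the regression that compares treatment periods, without defining it and with a later clause that leaves it out. Under either class-based reading the onset ratio is distorted when there is no onset effect: about 1.1-1.2 for elapsed classes with the planning contrast confined to the 4 weeks stated, up to about 1.5 only if it persists through the off-treatment year, and about 0.75-0.85 for completed length when a death ends the episode. The direction follows from the protocol's own classes and planning rates. The size rests on assumed treatment numbers and duration mix, on one duration effect shared by on- and off-treatment time, and on reading the planning percentages as annual rates. Linear elapsed duration does little harm. The finding concerns the onset ratio and what is built on it, not the comparison of the two drugs.

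**What to change.** In the model that yields the onset and off-treatment rate ratios, do not enter duration as a main effect common to on- and off-treatment time. Define mutually exclusive states:

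- On treatment, by time since the start: weeks 1-4, then later bands (for example weeks 5-26, 27-52 and beyond 52), with the reference for the onset ratio named.
- Off treatment: weeks 1-4 and weeks 5-52, each split by the completed duration of the episode just ended. Duration is then known before the time at risk begins, and the planned comparison of short with long treatment is estimated directly.

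State in the same paragraph whether the adjusted period ratios condition on anything beyond the confounder list. Leaving duration out of the period model, or letting it act only off treatment, returned 1.00 in the check above.

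The cost is a change of wording, a few more rate parameters, and slightly wider intervals in the finer bands. No extra data are needed.

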*Main outcome:* All and cause specific death (in particular drug poisoning/overdose) during drug treatment or follow-up period up to one year after date of last opiate substitution treatment (OST) prescription/treatment admission. Standard codes for drug related poisonings deaths will be used to define overdose deaths (23): ICD-10 codes: F11-16; F18-19; X40-44; X60-64; X85; Y10-14; as well as in terms of general and specific drugs mentioned on the death certificate (any opiate, heroin and Morphine, Methadone, buprenorphine, dihydrocodeine, other opiods, cocaine, all amphetamines and MDMA, GHB, GBL, all benzodiazepines, barbiturates, all antidepressants, paracetamol and other over the counter medicines). We will categorise deaths as “avoidable” and “preventable” based on ONS definitions (<http://www.ons.gov.uk/ons/publications/re-reference-tables.html?edition=tcm%3A77-262418>). Other specific causes that will be investigated include suicide and other injury (non drug related poisoning), infectious diseases, cirrhosis and liver disease. All cause mortality will be expressed as a rate and as a Standardised Mortality Ratio (SMR) compared to standard age and sex death rates for England and Wales. Cause specific mortality will be expressed as rates – and SMRs also will be calculated for non-drug related poisonings. Follow-up of patients extracted from primary care database (Clinical Practice Research Datalink, CRPD) will be from date of first OST prescription within risk period beginning 1990 to end 2011. A patient’s follow up will cease either one year after the expiry of their last prescription for OST or the date of death or on the date of transfer out from the general practice or risk study period end (which ever date occurs first). [Follow-up of patients extracted from Drug Data Warehouse (DDW) will be from 2005 to 2009 the period for which National Drug Treatment records are linked to the mortality register.] We are censoring follow-up twelve months after last prescription or specialist drug treatment date in order to reduce potential bias.

Secondary outcomes concern the practice and delivery of OST including:- annual number of people in OST; modality/specific OST drug; duration of OST; dose; evidence of reaching optimal dosage, tapering OST dose towards planned discharge, and supervised consumption; and co-prescription of benzodiazepines.

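### The propensity-matched comparison of short and long treatment has no time zero, and under the protocol's own follow-up and duration rules it carries immortal-time bias

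*Protocol*

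**What the plan says.** Four places in the protocol bear on this.

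- **Data/ Statistical Analysis Plan, item 1, second analysis.** Propensity scores will be used to "match the patients exposed either to buprenorphine or methadone or to short or long term treatment". The paragraph does not define short and long, and gives neither an index date nor a risk window for that comparison.
- **Exposures, outcomes and covariates, Exposure.** For each treatment period the study will "classify treatment duration (≤ 1 month, 2-6 months, 7-12 months, 12+months"), that is, by the length observed.
- **Exposures, outcomes and covariates, Main outcome.** Follow-up "will be from date of first OST prescription within risk period" and ends at the earliest of several dates, among them "one year after the expiry of their last prescription for OST or the date of death".
- **Data/ Statistical Analysis Plan, item 1, first analysis.** The Poisson regression is described as "incorporating time varying covariates (such as co-prescription of benzodiazepines, episode and duration of treatment"). Duration is therefore time-varying there. The matching paragraph does not carry this over.

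One further place specifies a short/long contrast. The Sample size/power calculation section compares the risk of death in the 4 weeks after treatment, with figures of 4.6% and 3.0%. The two groups in that contrast are described by the words "for people treated for short duration of treatment (< 1 month) compared to those treated for 12 months or longer". The number needed per arm of this contrast is put at 3123.

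**The concern.** Observed treatment length is known only when treatment ends, and death is one of the things that ends it. If patients are grouped by that length and followed from their first prescription, survival decides group membership. The 12+ month group has 12 months in which, by definition, nobody can die, while every on-treatment death in month 1 is assigned to the short group. A propensity score balances characteristics at entry. It cannot balance a group label that depends on what happens afterwards.

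Two things are at stake. First, treatment duration heads the list of modifiable factors in the protocol's over-arching hypotheses, so a false protective effect of long treatment would bear on a question the study was set up to answer. Second, the plan intends to read agreement or disagreement between its several methods as evidence on residual confounding. An artefact of time zero in one method would be mistaken for confounding handled differently by the others.

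**Working it through.** **1. The protocol's own short/long figure.** Inputs: 4.6% and 3.0% (Sample size/power calculation). Two-sided 5% and 90% power are assumed; the section states power above 90% at the head of its list and no alpha.

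n = [1.960·√(2·0.038·0.962) + 1.282·√(0.046·0.954 + 0.030·0.970)]² / 0.016² = 2999 per group.

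With continuity correction: (2999/4)·[1 + √(1 + 4/(2999·0.016))]² = 3123, the stated value. This figure belongs to a contrast whose risk window opens after treatment ends, when duration is already known.

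**2. What the follow-up and banding rules do to a match from first prescription.** Take a null case in which duration has no effect.

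Inputs:
- Death rate λ = 0.0069 per year on and off treatment. This is the 0.69% given for methadone in the sample size section, read as per person-year (assumption).
- Stopping rate μ = 0.5, 1, 2 or 4 per year (assumption).
- One treatment period per patient (simplification).
- Follow-up to one year after treatment end (Main outcome paragraph).

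Formulas, with Λ = λ + μ:
- Share of treatments ended by death, the same at every length: p = λ/Λ.
- Mean length of treatments up to 1 month: E_S = 1/Λ − (1/12)e^(−Λ/12)/(1 − e^(−Λ/12)).
- Mean length of treatments over 12 months: E_L = 1 + 1/Λ.
- Off-treatment year: q = 1 − e^(−λ) = 0.00688. Deaths per treatment d = p + (1 − p)q. Off-treatment person-years y = (1 − p)q/λ.
- Rate in each group = d/(E + y). Because d is the same in both groups, the ratio is (E_L + y)/(E_S + y).
- On-treatment time only: rate = p/E, ratio = E_L/E_S.

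Worked at μ = 1: Λ = 1.0069, p = 0.00685, E_S = 0.0411, E_L = 1.993, d = 0.01368, y = 0.990. Rates are 0.01368/1.031 = 1.33 and 0.01368/2.983 = 0.46 per 100 person-years, ratio 2.9.

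| Stops per year | Short, full follow-up | Long, full follow-up | Ratio | On-treatment only, short vs long | Ratio |
|---|---|---|---|---|---|
| 0.5 | 1.99 | 0.52 | 3.9 | 32.9 vs 0.46 | 72 |
| 1 | 1.33 | 0.46 | 2.9 | 16.7 vs 0.34 | 49 |
| 2 | 1.00 | 0.41 | 2.4 | 8.5 vs 0.23 | 37 |
| 4 | 0.83 | 0.38 | 2.2 | 4.4 vs 0.14 | 32 |

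(Rates are deaths per 100 person-years; the true ratio is 1.00 throughout.)

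**3. A different duration distribution.** With planned duration lognormal and independent of hazard, and the same follow-up rule, the false ratio is 2.05 at a median of 4 months and log-SD 1.3 (1.02 vs 0.50 per 100 person-years). Over medians of 2 to 12 months and log-SDs of 1.0 to 1.6 it runs from about 1.5 to 18. Hazards of 0.35 to 1.2 per 100 person-years barely change it.

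**4. Time zero at treatment end.** Both groups then enter alive with their duration fixed and face the same λ, so the ratio under this null is 1.00.

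**5. Scale.** The planned short/long difference is a ratio of 4.6/3.0 = 1.53. It concerns another window, and as worded the lower risk is in the short-treatment group. The artefact of about 2.2 to 3.9 is larger, and it raises the rate in the short group.

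**The case against.** The strongest defence is that the matching paragraph never says deaths are counted from the start of treatment. The one short/long contrast the protocol specifies opens its window at treatment end, and an index date for a supporting analysis is commonly left to a statistical analysis plan. This stands in part: the bias follows from reading the matching paragraph with the general follow-up rule, and is not stated in that paragraph. But the protocol itself fixes the contrast, the bands and the start of follow-up, and nothing limits the match to the post-treatment window. Applied as written, these rules produce the bias, so this is more than detail left for later.

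Three stronger readings are tempting and should not be drawn.

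- **A 32- to 72-fold distortion.** That range holds only if on-treatment time alone is counted. The protocol follows patients for a further year, which brings the ratio down to 2.2 to 3.9 under the same assumptions.
- **The drug comparison is affected too, through patients who switch.** The protocol expects changes in type of OST, but it classifies exposure by treatment period. No stated rule credits time before a switch to the later drug.
- **The biased estimate enters the policy model.** The model section takes effects for periods on or off treatment from the CPRD and DDW analyses. It does not say that the matched short/long estimate is one of them.

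It is also fair to note that duration is handled soundly as time-varying in the Poisson analysis, and that methadone against buprenorphine, not duration, is the key hypothesis.

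**Conclusion.** The point holds for the matched short/long comparison only. Under the follow-up start and duration bands that the protocol states, that comparison would show excess mortality with short treatment when there is none: about 2.2- to 3.9-fold, and 2.9-fold at one stop per year. This rests on a constant hazard of 0.69 per 100 person-years on and off treatment, assumed stopping rates of 0.5 to 4 per year, and one treatment period per patient. The protocol gives no duration distribution, and lognormal alternatives widen the range to about 1.5 to 18. The direction does not depend on these choices. The post-treatment contrast in the sample size section and its 3123 per group, the Poisson analysis and the buprenorphine/methadone match are not affected.

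**What to change.** In the second analysis of the Data/ Statistical Analysis Plan:

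1. Start the matched short/long comparison at treatment end, define short and long there, and build the score from data up to that date.
2. Compare only the post-treatment windows the plan already uses, weeks 1-4 and weeks 5-52. This agrees with the contrast in the sample size section and leaves 3123 per group unchanged.
3. For effects of duration during treatment, rely on time-varying duration as in the Poisson analysis, so that each day counts in the duration reached by that day.

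The cost is a few sentences and re-indexing of data already held. There are two downsides, which the protocol should state. There would be no matched short/long contrast during treatment. The post-treatment comparison would also be conditional on surviving to treatment end: the long group has survived at least 12 months on treatment, so some selection remains and should be acknowledged in interpretation.
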